### 2.9. Statistical Analysis 

Descriptive statistical analyses will be conducted to investigate the baseline characteristics of the sample. To evaluate differences between the two groups (ACT + TAU vs. TAU only) across the two time points (pre—Time 0/week 1; post—Time 1/week 3 psychological intervention), repeated measure between groups ANOVAs will be performed for each dependent variable—namely, AFQ-Y, PWB, DASS-21, DERS, and DEBQ. In this case, a global effect size (Cohen’s f and/or eta-squared—η^2^) will be used to quantify the [global] difference of the two groups across times. Global effects size will be interpreted with the following benchmarks [63]: null (*f* < 0.10; η^2^ < 0.003); small (f from 0.10 to 0.25; η^2^ from 0.003 to 0.039); moderate (*f* from 0.25 to 0.40; η^2^ from 0.40 to 0.110); and large (*f* ≥ 0.40; η^2^ > 0.110). Moreover, several focused comparisons will be performed to assess differences both within and between groups. In particular, differences between the two groups will be assessed using an independent samples t-test both at the baseline as well as at the end of psychological treatment, separately—namely, T1: ACT + TAU vs. TAU and T2: ACT + TAU vs. TAU. Conversely, differences within each group across the two time points will be assessed using dependent samples t-test—namely, ACT + TAU: T1 vs. T2; and TAU: T1 vs. T2. The magnitude of the differences will be interpreted by using the Cohen’s d [64]—more in detail, for between-groups comparisons, the classical Cohen’s d formula will be used; in contrast, for within-groups comparisons, the modified formula for dependent data will be used. Each Cohen’s d will be interpreted using the following benchmarks: null (*d* < 0.20), small (d from 0.20 to 0.49), moderate (d from 0.50 to 0.79), and strong (*d* > 0.80). 

Participants who reported missing data as well as subjects who will not participate in each therapy session will be excluded from the final sample, and thus, their data will not be analyzed. Moreover, also, participants who drop out from the program will be excluded from the final sample. 

Analyses will be carried out using Jamovi (version 1.6.15) [64].

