## Abstract

This Randomized Controlled Trial [(RCT) aims to evaluate the effectiveness of a brief Acceptance and Commitment Therapy (ACT)-based intervention combined with treatment as usual (TAU) compared to TAU only in improving psychological conditions in a sample of adolescents with obesity (body mass index, BMI > 97th percentile for age and sex) within the context of a wider multidisciplinary rehabilitation program for weight loss. Fifty consecutive adolescents (12–17 years) of both genders with obesity will be recruited among the patients hospitalized in a clinical center for obesity rehabilitation and randomly allocated into two experimental conditions: ACT + TAU vs. TAU only. Both groups will attend a three-week in-hospital multidisciplinary rehabilitation program for weight loss. The ACT + TAU condition comprises a psychological intervention based on ACT combined with a standard psychological assessment and support to the hospitalization. The TAU comprises the standard psychological assessment and support to the hospitalization. At pre- to post-psychological intervention, participants will complete the Avoidance and Fusion Questionnaire for Youth, the Psychological Well-Being Scale, the Depression Anxiety Stress Scale, the Difficulties in Emotion Regulation Scale, and the Emotional Eating subscale of the Dutch Eating Behavior Questionnaire to assess psychological well-being as the primary outcome and experiential avoidance, psychological distress, emotional dysregulation, and emotional eating as secondary outcomes. Repeated-measures ANOVAs (2 × 2) will be conducted. The study will assess the effectiveness of a brief ACT-based intervention for adolescents with obesity in improving their psychological conditions by targeting specific core processes of the ACT framework (openness, awareness, and engagement). Future directions of the study will assess whether these psychological processes will contribute to addressing long-term weight loss.

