### 2.3. Measures

All demographical (gender, age, nationality, educational level, and family composition) and clinical data will be collected via self-report using Italian validated and widely used questionnaires. The following psychological measures will be collected pre (Time 0/week 1) and post (Time 1/week 3) psychological intervention. 

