### 2.4. Randomization Procedure

Participants will be randomly assigned to the experimental (ACT+ TAU) or control (TAU) group. We will perform simple randomization with a 1:1 allocation ratio using the web site Randomization.com (http://www.randomization.com) (accessed on 8 June 2021). Randomization will occur after the baseline measurements in order to ensure similar baseline characteristics of groups.

Allocation concealment will be ensured, since all the patients will generate an anonymous code that will be associated with the randomization generated by the program. Researchers will be blind to the association made.

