### 2.8. Sample Size Calculation

In line with previous studies [60,61] to calculate the sample size, an a priori power analysis was carried out using the software G.Power 3.1.9.4 [62]. 

The required sample size was computed for an analysis of variance (ANOVA) with 2 groups (between variable; ACT + TAU vs. TAU) × 2 times (within variable; Time 0/Time 1). To the best of the author’s knowledge, no other similar studies are available in the literature. Therefore, the a priori effect size (Cohen’s *f*) for the global effect (groups x time) was set to 0.2 (small effect size) [63]. Moreover, the Type I error [α] probability was set to 0.05, and the power [1-β] was set to 0.95. In addition, correlation among repeated measures to 0.3 (small–moderate correlation/linear effect). Non-sphericity was assumed, and it was set to 1. Results showed that there is a more than 95% chance of correctly rejecting the null hypothesis of no significant effect of the interaction with an overall sample of 116 subjects: a minimum of 58 participants per group.

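### The planned 2 × 2 repeated-measures ANOVA is a change-score test; at the protocol's own correlation of 0.3 it is less precise than ignoring baseline and needs 116 patients where ANCOVA needs 76

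*Protocol article*

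**What the plan says.** The confirmatory model is fixed in three places of the protocol article. The Abstract says "Repeated-measures ANOVAs (2 × 2) will be conducted". Section 2.9 says "repeated measure between groups ANOVAs will be performed for each dependent variable", the outcomes being AFQ-Y, PWB, DASS-21, DERS and DEBQ. Section 2.8 sizes the trial for the same model: "The required sample size was computed for an analysis of variance (ANOVA) with 2 groups" and two times, with a Cohen's f that "for the global effect (groups x time) was set to 0.2 (small effect size"), alpha 0.05, power 0.95 and "correlation among repeated measures to 0.3". The result is 116 patients, 58 per arm.

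Section 2.3 confirms that there are only two assessments, week 1 and week 3. Section 2.4 says that "Randomization will occur after the baseline measurements".

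The only other between-arm comparisons in section 2.9 are unadjusted t-tests, one at baseline and one at the end of treatment. No analysis uses the baseline score as a covariate.

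**The concern.** With two arms and two time points, the repeated-measures ANOVA adds nothing to a comparison of raw changes: its interaction F is the square of the change-score t. Subtracting the baseline helps only when the two scores are strongly correlated. At a weak correlation such as 0.3, it adds more baseline noise than it removes between-patient variation. The baseline is collected before allocation in every patient, so it is a legitimate covariate that costs nothing to use.

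Two things are at stake. The first is power and interval width on the primary outcome. The second is the estimate when the arms differ at baseline by chance: the arm that starts lower tends to improve more through regression to the mean, and a change score counts that as treatment effect.

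**Working it through.** **Inputs.** From section 2.8: f = 0.2, alpha = 0.05, power = 0.95, correlation ρ = 0.3, non-sphericity 1, N = 116. From section 2.4: 1:1 allocation. From the Abstract: N = 50. Assumption not in the protocol: the same SD at both times.

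**1. Reproduce 116.** For the interaction, the noncentrality is λ = f²·N·m/(1−ρ) with m = 2 times and df = (1, N−2). At N = 116, λ = 0.04 × 116 × 2/0.7 = 13.26 and power is 95.06%. The smallest even N reaching 95% is 116, so the stated figure is right for the planned test.

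**2. Show that it is a change-score test.** In a 2 × 2 layout, f = 0.2 means a between-arm difference in mean change of 4f = 0.8 SD. The variance of a change is 2(1−ρ)SD² = 1.40 SD². The t-test noncentrality squared is 0.8² × 116/(4 × 1.40) = 13.26, the same value, and power is again 95.06%. On a simulated data set, the interaction F and the squared change-score t were both 0.7943.

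**3. Compare three analyses of the same data at ρ = 0.3.** Power comes from the noncentral t with λ = d²N/(4V), where V is the variance factor in the table and d the difference in SD units. The df are N−2, or N−3 for ANCOVA.

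| | Change (planned) | Time 1 only | ANCOVA |
|---|---|---|---|
| Variance factor V | 2(1−ρ) = 1.40 | 1.00 | 1−ρ² = 0.91 |
| N for 95% power at 0.8 SD | 116 | 84 | 76 |
| Power, N = 116, 0.8 SD | 95.1% | 99.0% | 99.4% |
| Power, N = 50, 0.8 SD | 64.9% | 79.2% | 82.7% |
| Power, N = 116, 0.5 SD | 61.7% | 76.1% | 79.9% |
| 80%-detectable difference, N = 116 | 0.62 SD | 0.53 SD | 0.50 SD |
| 80%-detectable difference, N = 50 | 0.96 SD | 0.81 SD | 0.77 SD |

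The 0.5 SD row is an illustrative smaller effect, not a protocol figure. A simulation of 4,000 trials with 58 per arm gave variance factors of 1.35, 0.99 and 0.89, and an ANCOVA-to-change ratio of 0.66.

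**4. Dependence on ρ.** The ratio of ANCOVA to change-score variance is (1−ρ²)/[2(1−ρ)] = (1+ρ)/2. Section 2.8 gives no source for 0.3. The test-retest values in section 2.3.1 run from 0.21 to 0.82 across the PWB subscales, and section 2.3.2 gives 0.64 for AFQ-Y.

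| ρ | (1+ρ)/2 | Saving | Power at N = 50, 0.8 SD: change → ANCOVA |
|---|---|---|---|
| 0.21 | 0.605 | 39.5% | 59.7% → 80.9% |
| 0.30 | 0.65 | 35% | 64.9% → 82.7% |
| 0.50 | 0.75 | 25% | 79.2% → 89.2% |
| 0.64 | 0.82 | 18% | 90.4% → 95.0% |
| 0.70 | 0.85 | 15% | 94.7% → 97.3% |
| 0.82 | 0.91 | 9% | 99.6% → 99.8% |

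The change score is worse than the Time 1 score alone when 2(1−ρ) > 1, that is, when ρ < 0.5.

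**5. Chance imbalance at baseline.** The standard error of the baseline difference is √(4/N) SD: 0.283 at N = 50 and 0.186 at N = 116. The chance of a difference above 0.2 SD in either direction is therefore about 48% and 28%. Given an imbalance δ, the change-score estimate shifts by −(1−ρ)δ. For δ = 0.2 SD and ρ = 0.3 that is 0.7 × 0.2 = 0.14 SD. ANCOVA removes this shift.

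**The case against.** The strongest reply is that nothing here is wrong. The planned test holds its type I error, is unbiased over repeated randomisation, and has a sample size that matches it. With the protocol's own 116 patients and 0.8 SD effect, ANCOVA raises power only from 95.1% to 99.4%. The larger gains need a smaller effect, or the 50 patients of the Abstract, and the conflict between 50 and 116 is a separate problem. This stands, and it makes the point one of efficiency.

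The second reply is that 0.3 is unsourced and may be low. Four of the six PWB test-retest values lie near 0.8, and the mean of the six is about 0.62. At 0.62 the saving is 19%, and the change score beats Time 1 alone (88.9% against 79.1% power at N = 50 and 0.8 SD). This also stands as a limit on size. The retest interval is not given, however, and 0.3 is the value the protocol chose for planning. ANCOVA remains the more precise analysis at every value below 1.

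Third, section 2.9 already includes an end-of-treatment t-test. That comparison is unadjusted and is a follow-up to the ANOVA, so it does not replace a baseline-adjusted primary estimate.

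Fourth, simple randomisation is not the cause of the imbalance. Unstratified blocking would leave chance differences in mean baseline score much the same. That is correct: the imbalance is ordinary chance at these sample sizes, and the argument for adjustment does not depend on the randomisation method.

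**Conclusion.** The concern holds. The primary test is a comparison of raw changes. Under the protocol's own correlation of 0.3 and equal SDs, its variance is 40% above that of the Time 1 score alone (1.40 against 1.00) and 54% above that of ANCOVA (1.40/0.91 = 1.54). About a third of the sample is lost (116 against 76), and 50 patients analysed as planned are worth about 50 × 0.65 = 32.5 under ANCOVA.

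The size of the loss rests on ρ: from about 40% at 0.21 to 9% at 0.82, the range of the PWB test-retest values in the protocol. The statement that the planned test is worse than ignoring baseline holds only below 0.5. The direction of the recommendation does not depend on ρ. This is a loss of precision and of protection against observed baseline imbalance; the planned test is not biased over repeated randomisation and the sample size contains no arithmetic error. The change should be made.

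**What to change.** In section 2.9 and the Abstract, replace the repeated-measures ANOVA as the primary analysis with a linear model of the Time 1 PWB total on arm, with the Time 0 PWB total as covariate. Report the adjusted mean difference with its 95% confidence interval and p-value. Section 2.3.1 describes six dimensions without naming the score to be analysed, so the text should also name the total explicitly. Use the same model for AFQ-Y, DASS-21, DERS and DEBQ, each with its own baseline.

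Restate section 2.8 for this model: give the target difference in SD units, the variance factor 1−ρ², and results over a range of ρ, since 0.3 has no stated source.

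The cost is wording only. Both scores are already collected, and the model uses one more degree of freedom than the change-score test.

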### 2.5. Procedures 

The trial will be conducted within the context of a three-week in-hospital multidisciplinary rehabilitation program for weight loss based on nutritional, physical, and psychological rehabilitation [50,51,52], according to the Italian National Health System recommendations. As part of the nutritional program, adolescents will be assessed by a staff dietician and placed on an individualized hypocaloric diet composed of 53% carbohydrates, 26% fat, and 21% protein [53] and a fluid intake of at least 1500 mL per day^−1^. They will also follow a daily nutritional counseling program provided both in individual and group settings, comprising dietetics lessons. As for physical rehabilitation, young patients will participate in a physical activity program consisting of five group training sessions per week lasting about 45–60 min per day of physical therapy comprising aerobic activities such as walking and cycling under the supervision of a therapist. The physical program also entails 2 h per week of aerobic leisure activities. As far as the psychological component is concerned, patients will take part in psychological counseling sessions that are provided at least once a week lasting about one hour each, carried out by a clinical psychologist, and aimed at promoting a healthy lifestyle and addressing psychological factors related to the onset of dysfunctional lifestyle habits. 

At week 1 of the hospitalization, all the patients will be screened for admission to the study with a clinical interview conducted by a clinical psychologist blinded to research aims to provide information about the study and assess the eligibility criteria according to the Diagnostic and Statistical Manual of Mental Disorders (DSM-5). Weight and height, to calculate BMI, will be measured by the internal medical team. Once we obtain informed consent to participate from parents and written assent from participants, young patients recruited for the study will be randomly assigned into two conditions. The experimental group will attend TAU plus a brief ACT-based intervention that comprises three sessions, provided once a week, lasting about one hour each, while the control group will attend TAU only. 

At pre (Time 0/week 1) and post-psychological intervention (Time 1/week 3), patients of both conditions will be invited to fill the questionnaires under the supervision of a member of the research team. 

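### Section 2.9 adjusts no between-arm comparison for sex, age or BMI, although all three are in hand at baseline and simple randomisation does not balance them; pre-specifying them is a cheap, minor improvement.

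*Protocol article*

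**What the plan says.** **Analysis.** Section 2.9 states that "repeated measure between groups ANOVAs will be performed for each dependent variable", with two groups and two time points. It adds independent-samples t-tests between arms at baseline and at the end of treatment, paired t-tests within each arm, and Cohen's d for each. No covariate appears in any of these. Baseline characteristics are used only for description.

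**Data in hand.** Section 2.3: "All demographical (gender, age, nationality, educational level, and family composition) and clinical data will be collected". Section 2.5: "Weight and height, to calculate BMI, will be measured by the internal medical team"; the sentence before it places screening in week 1.

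**Allocation.** Section 2.4: "We will perform simple randomization with a 1:1 allocation ratio". No stratification factor is named. The same section relies on the timing of randomisation, after the baseline measurements, to make the arms similar.

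**Planning inputs.** Section 2.8 sets Cohen's f = 0.2 for the group x time effect, "correlation among repeated measures to 0.3", and "probability was set to 0.05, and the power [1-β] was set to 0.95". It arrives at 116 participants, 58 per arm. The abstract gives fifty.

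**The concern.** Randomising after the baseline assessment guards against some problems, but it does not make the arms alike. Simple randomisation leaves balance on sex, age and BMI to chance, and the analysis does nothing further about it. In a trial of this size, with both sexes and ages from 12 to 17, the arms may differ visibly on one of these.

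Two things are at stake. The first is interpretation. Section 2.9 compares the arms at baseline on each scale but gives no rule for what follows, so if a difference in sex or age shows up, any adjustment would be chosen after the data were seen. The second is precision. Any variance that these variables explain, and that the analysis could have removed, stays in the error term.

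Section 2.9 states its tests outright. The point is therefore about a stated analysis choice, not about detail that a condensed article leaves to another document.

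**Working it through.** **1. The plan's own figure.** Inputs from section 2.8: f = 0.2, correlation rho = 0.3, alpha = 0.05, m = 2 times, sphericity correction 1. For the within-between interaction, lambda = f² x N x m / (1 - rho), with 1 and N - 2 degrees of freedom.
- N = 116: lambda = 0.04 x 116 x 2 / 0.7 = 13.26, power 95.06%.
- N = 114: power 94.7%.

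The smallest even N is 116, so the stated figure reproduces. At the abstract's N = 50, lambda = 5.71 and power is 64.9%.

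**2. What the group x time test is.** With two times it equals a two-sample t-test on change. In units of the SD at one time point, the variance of change is 2(1 - 0.3) = 1.4, and f = 0.2 corresponds to a difference in mean change of 0.8. A covariate that shifts a participant's score equally at both times drops out of the change. Only an effect on the change itself remains. The end-of-treatment t-test has no such protection.

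**3. How often imbalance arises.** Assumptions, since the article gives neither distribution: half are girls; ages are spread evenly over the whole years 12 to 17, so SD = sqrt(35/12) = 1.71. Sex is simulated with 400,000 simple randomisations. Age uses SE = 1.71 x sqrt(4/N).

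| | N = 116 | N = 50 |
|---|---|---|
| Sex differs by at least 10 points | 29% | 49% |
| Sex differs by at least 15 points | 11% | 31% |
| Mean age differs by at least 0.5 year | 11% | 30% |

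The normal approximation for the 10-point row gives 28% and 48%.

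**4. Validity without covariates.** With an unadjusted covariate that does predict change (slope 0.4 per SD), 20,000 simulated null trials at each size rejected in 4.8% of runs, at both N = 50 and N = 116. Chance imbalance does not raise the type I error.

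**5. Gain from adjusting.** Three covariates cost 3 degrees of freedom, so df2 = N - 5 and lambda is divided by (1 - R²). Here R² is the share of the variance of *change* explained. The article gives no value, so a range is shown.

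| R² of change (assumed) | Power, N = 116 | Power, N = 50 |
|---|---|---|
| No covariates | 95.06% | 64.9% |
| 0 | 95.05% | 64.8% |
| 5% | 95.9% | 67.0% |
| 10% | 96.7% | 69.3% |
| 15% | 97.5% | 71.8% |

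**6. How demanding those R² values are.** If sex alone (half and half) supplied R², the mean change of girls and boys would have to differ by 2 x sqrt(1.4 x R²), that is 0.53, 0.75 or 0.92 SD for R² = 5%, 10% or 15%. The whole planned treatment effect is 0.8 SD.

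**7. Shift from one realised imbalance.** A 10-point sex imbalance with a 0.75 SD sex difference in change moves the group x time estimate by 0.10 x 0.75 = 0.075 SD. Its standard error at N = 116 is sqrt(1.4 x 4/116) = 0.22, so the shift is about a third of a standard error and about 9% of the planned effect (0.075/0.8).

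**The case against.** The strongest case against is that nothing here is an error. The planned test keeps its type I error, randomisation makes the estimate unbiased over repeated allocations, and no passage says that sex, age or BMI predicts change in well-being. BMI is also range-restricted by eligibility (above the 97th centile). Reaching R² of 5% or more would take sex-by-time effects that are large beside the treatment effect. Using the Time 0 score as a covariate would gain more: at rho = 0.3 the error variance would be 1 - 0.3² = 0.91 instead of 1.40. All of this stands. It limits the point to a minor one, and the Time 0 score is a separate matter.

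Some stronger readings are tempting, and the documents do not support them:

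- *Imbalance in sex, age or BMI stays in the primary result.* Not for stable effects, which cancel in the group x time test. It holds in full only for the end-of-treatment t-test and its Cohen's d.
- *Visible imbalance is likely.* At N = 116 the sex difference is under 10 points in about 71% of allocations, and the mean age difference is under half a year in about 89%. Plausible is the right word. At the abstract's 50 the sex figure comes close to even odds.
- *At a correlation of 0.3 the Time 0 score explains only 9% of Time 1 variance, so much is left for these covariates.* The remainder may be measurement noise; section 2.3.1 reports test-retest correlations of 0.21 and 0.31 for two subscales of the primary scale.

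What the objection does not remove is that the data are already collected, the cost is close to nil even if the gain is zero, and a covariate set fixed in advance closes off adjustment chosen after the fact.

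**Conclusion.** The point holds as a minor one. Every comparison in section 2.9 is unadjusted, while three baseline variables that the design leaves to chance are available. The planned tests are valid, so this concerns precision and interpretation given the realised allocation; it does not correct a faulty test.

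For the group x time test the benefit runs from nothing to about 2.4 percentage points of power at N = 116 (95.06% to 97.5%), and to about 7 points at N = 50 (64.9% to 71.8%), for R² of change from 0 to 15%. That range is an assumption, as are the even sex split and the even age spread behind the imbalance figures. The case is firmer for the end-of-treatment comparison, where stable covariate effects do not cancel, but the article gives no figure from which to size it.

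**What to change.** In section 2.9, name sex, age and baseline BMI in advance as covariates in the model that gives the between-arm estimate for PWB and for each secondary scale.

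- If the 2 x 2 ANOVA is kept, enter each with its covariate-by-time term. A covariate main effect alone leaves the group x time test unchanged.
- If a Time 1 model adjusted for the Time 0 score is used instead, enter them as main effects.
- Keep the unadjusted result as a sensitivity analysis.

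The cost is one sentence and three degrees of freedom, with no new data, visits or participants. If the covariates do not predict change there is no gain, and the loss is slight: 95.06% to 95.05% power at N = 116, 64.9% to 64.8% at N = 50.

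### The moderate eta-squared band is inverted and the eta-squared cut-offs do not match the paired Cohen's f cut-offs, so the size label can depend on the metric

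*Protocol article*

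**What the plan says.** Section 2.9 (Statistical Analysis) plans a repeated-measures between-groups ANOVA for each of AFQ-Y, PWB, DASS-21, DERS and DEBQ. For these it states that "a global effect size (Cohen’s f and/or eta-squared—η^2^) will be used to quantify the [global] difference of the two groups across times". Four labels follow, each with a band on both scales:

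- The lowest label applies when f is below 0.10 or eta-squared is below 0.003, and is called null.
- The second label is given as "small (f from 0.10 to 0.25; η^2^ from 0.003 to 0.039", with the upper limit on each scale closing the band.
- The third label is where the eta-squared limits run downwards: "moderate (*f* from 0.25 to 0.40; η^2^ from 0.40 to 0.110".
- The highest label, large, starts at an f of 0.40 and, on the other scale, above an eta-squared of 0.110.

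The section does not say whether eta-squared is partial or classical, which error term f is built on, or which metric decides the label if the two disagree.

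**The concern.** Two sets of cut-offs that share one set of labels have to place the same result in the same band. Here one band is empty as printed, and the remaining eta-squared limits do not look like conversions of the f limits beside them. These are the stated rules for describing the size of the group-by-time effect on the primary outcome (PWB) and on the four secondary outcomes. If the scales disagree and either may be used, one analysis can be reported under two different size labels, and nothing in the plan settles which.

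**Working it through.** **Inputs, all from section 2.9.** f cut-offs: 0.10, 0.25, 0.40. Eta-squared cut-offs: 0.003, 0.039, 0.110. Printed lower limit of the moderate eta-squared band: 0.40.

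**Step 1: the moderate band.** Since 0.40 > 0.110, no value lies in the interval. As printed, small ends at 0.039 and large begins above 0.110, so everything between has no label, and 0.40 itself falls under large. The preceding limit of 0.039 suggests that 0.040 was meant.

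**Step 2: do the cut-offs match?** If f and eta-squared use the same error term (partial eta-squared), then eta² = f²/(1 + f²) and f = √[eta²/(1 − eta²)].

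| f cut-off | eta² by conversion | eta² printed | f implied by the printed eta² |
|---|---|---|---|
| 0.10 | 0.0100/1.0100 = 0.0099 | 0.003 | √(0.003/0.997) = 0.055 |
| 0.25 | 0.0625/1.0625 = 0.0588 | 0.039 | √(0.039/0.961) = 0.201 |
| 0.40 | 0.1600/1.1600 = 0.1379 | 0.110 | √(0.110/0.890) = 0.352 |

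None of the three printed values is reproduced.

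**Step 3: where the labels conflict, under the same assumption.**

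| f | eta² | label by f | label by eta², 0.40 read as 0.040 | label by eta², as printed |
|---|---|---|---|---|
| 0.08 | 0.0064 | null | small | small |
| 0.22 | 0.0462 | small | moderate | none |
| 0.30 | 0.0826 | moderate | moderate | none |
| 0.37 | 0.1204 | moderate | large | large |

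The conflict ranges are f of about 0.055 to 0.10, 0.20 to 0.25, and 0.35 to 0.40. Elsewhere the scales agree once 0.40 is read as 0.040. As printed, f of about 0.20 to 0.35 has no eta-squared label at all.

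**Step 4: would another definition reconcile them?**

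- *Partial eta-squared with f on the convention that reproduces the sample size in section 2.8* (two time points, correlation 0.3). Here f² is replaced by 2f²/(1 − 0.3). The three f cut-offs give 0.028, 0.152 and 0.314, further from the printed values.
- *Classical eta-squared with f on the within-subject error.* With correlation 0.3 and no other effects, within-subject error is (1 − 0.3)/2 = 0.35 of the non-effect variance, so eta² = f²/(1/0.35 + f²). f = 0.10 gives 0.0100/2.867 = 0.0035, f = 0.25 gives 0.0625/2.920 = 0.021, and f = 0.40 gives 0.1600/3.017 = 0.053. The first is near the printed 0.003, but the other two are about half the printed 0.039 and 0.110.
- *Classical eta-squared with an arbitrary amount of other variance.* The amount needed, relative to the error variance, is f²/eta² − 1 − f². That is 3.333 − 1.010 = 2.32, 1.603 − 1.0625 = 0.54 and 1.455 − 1.160 = 0.29 at the three cut-offs. One definition would need one amount.

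None of the definitions tried fits all three pairs.

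**Step 5: does this reach the sample size?** Section 2.8 uses f = 0.2, alpha 0.05, power 0.95 and correlation 0.3. With noncentrality f²·N·2/(1 − 0.3) and 1 and N − 2 degrees of freedom, the required N is 116 (power 0.9506), as stated. The labels play no part in it.

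**The case against.** The strongest objection is that the simple conversion has a condition: f and eta-squared must share an error term. The protocol names eta-squared without the word partial, in a 2 × 2 mixed design, where classical eta-squared also carries between-subject variance. This stands, and it limits what can be claimed:

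- A reader might infer that eta-squared always gives the same or a more flattering label. The document does not support that. In the classical calculation above, f = 0.25 is moderate by f but, at 0.021, small by eta-squared. f = 0.40 is large by f but, at 0.053, moderate (0.40 read as 0.040). The direction depends on a definition that is not given.
- A reader might also infer that the planning value, f = 0.2, sits at the edge of the moderate band because it converts to 0.0385. That uses the simple conversion. On the convention that reproduces N = 116, f = 0.2 implies a partial eta-squared of 0.1143/1.1143 = 0.103. No such statement about the planning value is safe.

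It can also be said that 0.40 is an evident slip for 0.040, that only verbal labels are affected, that the wording permits both metrics to be reported, and that the between-group and within-group comparisons have their own Cohen's d benchmarks. All of this is fair and keeps the point modest. It does not remove it: correcting the slip leaves the cut-offs unmatched, and the article prints these numbers as its rule, so condensation does not explain them. What the cited benchmark source says cannot be checked here, and the point does not rest on it.

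**Conclusion.** The point holds in a limited form. The inverted moderate band is an error whatever the definition: as printed, eta-squared above 0.039 and up to 0.110 has no label. The mismatch between the two sets of cut-offs also stands, because none of the definitions tried reconciles all three pairs. The exact conflict ranges (f of about 0.055 to 0.10, 0.20 to 0.25, and 0.35 to 0.40) assume that f and eta-squared share an error term and that 0.40 is read as 0.040.

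The consequence is one of interpretation. The size label for the group-by-time effect can depend on the metric chosen, and the plan leaves that choice open. The document does not show any intention to choose after seeing results, and the hypothesis test, alpha, power and N are untouched. It should be corrected because it is a stated rule in the analysis section covering the primary and secondary outcomes.

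**What to change.** In section 2.9:

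1. Replace the and/or wording with one governing metric for the size label.
2. Define that metric: partial or classical eta-squared, and the error term on which f is computed.
3. Give one matching set of cut-offs and correct the 0.40. For partial eta-squared with f on the same error term, the values matching f of 0.10, 0.25 and 0.40 are 0.010, 0.059 and 0.138. These should not be inserted without the definition, because on another convention for f the conflict would return.

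The cost is about one sentence of text. The downside is that some results will receive a different size label from the one the printed bands would give.
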